### Sample size

A meta-analysis on prosocial consequences of interpersonal synchrony among neurotypical adults found a medium-sized effect of interpersonal synchrony on prosociality with regard to both attitudes and behavior towards individuals or groups involved in the same intervention [28]. Therefore, an effect defined as d = 0.25 may be expected [49]. An a-priori power analysis using the G*Power computer program [50] indicated that a total sample size of 40 participants would be needed to detect medium-sized effects defined as f = 0.25, with 80% power and alpha at .05, using a repeated measure, within-between interaction ANOVA with four groups and three measurements. We will recruit at least N = 60 participants (30 in each intervention group) to plan for possible dropouts.

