#### Social closeness

Social closeness will be measured using the Inclusion of Other in Self Scale (IOS) [60, 61]. This scale is made up of seven Venn diagram-like pictures where one circle represents the participant and the other circle represents the entire intervention group. The diagrams, ranging from no overlap to near complete overlap, measure close relationships between self and the group by capturing aspects of both feeling close and behaving close. The scale has high reliability for the friendship subgroup sample (Cronbach’s alpha .92) and a high test-retest correlation (r = .86 (n = 31)). Significant correlations between the IOS and measures of closeness that are primarily verbal and multi-item were found (60).

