
*2*. *Public goods game*. Participants will be told they will be given 30 NIS and that they can donate some or all of it to a group investment, as described in [68]. The money in the group investment will then be doubled and divided equally among all members of the group. The money earned in this game will be compensation for participating in the study. In contrast to the collection task, participants’ contribution will be confidential to avoid group pressure. Cooperation on this task will be operationalized by the amount of money each participant decides to donate to the group investment.

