#### Quantitative data analysis

The data obtained as study variables will be coded, processed and analyzed at the end of the collection process. IBM SPSS Statistics Version 27 will be used for statistical analysis. To control the family-wise error rate when performing multiple hypothesis tests, Bonferroni Step-Down (Holm) procedure will be applied. Participants must attend at least 4 sessions to be included in the analyses. To describe the sample, descriptive statistics will be calculated followed by univariate and bivariate statistical analyses. The first step will be to assess whether the data follows a normal distribution for each of the variables which will guide the choice of parametric or non-parametric tests. To answer the primary study objective and the first secondary study objective, the effects of the intervention over time (at the end of the intervention and after 17 weeks) will be examined using a two-way mixed model ANOVA. To explore the second secondary study objective, the influence of the need to belong on the effect of the intervention over time (at the end of the intervention and after 17 weeks) will be examined using a three-way mixed model ANOVA.

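### A normality check on each variable is left to guide the choice of test, which conflicts with the mixed ANOVAs named for the primary outcomes and names no fallback that tests arm by time

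*Protocol article*

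**What the plan says.** All of this is in the protocol article.

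- **Quantitative data analysis.** After descriptive, univariate and bivariate statistics, the first step is to "assess whether the data follows a normal distribution for each of the variables which will guide the choice of parametric or non-parametric tests". The following sentences say that the intervention effect over time, for the primary objective and the first secondary objective, "will be examined using a two-way mixed model ANOVA", and that the influence of need to belong "will be examined using a three-way mixed model ANOVA". Neither sentence depends on the normality result. No non-parametric counterpart is named for either ANOVA.
- **Sample size.** The calculation is for a repeated-measures "within-between interaction ANOVA with four groups and three measurements".
- **Outcomes (Table 2 and the sections on each measure).** There are three primary outcomes. Confidential cooperation is "the amount of money each participant decides to donate to the group investment", out of 30 NIS, so it is bounded at 0 and 30. Work-related stress is an eight-item scale with items scored 1 to 7, so it is also bounded. Non-confidential cooperation is a step rate with no stated ceiling.

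**The concern.** Three things are wrong with the rule.

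1. **It examines the wrong quantity.** The ANOVA assumption concerns residuals. A real arm or time effect can by itself make a pooled variable look non-normal.
2. **It makes the test depend on the outcome data.** If it applies to a primary outcome, the confirmatory test is not fixed until that outcome has been inspected.
3. **Its second branch is empty.** The primary question and the power calculation both concern the arm-by-time effect. Friedman and Wilcoxon tests work within one arm, and Mann-Whitney at one visit uses no baseline. An analyst who follows the rule to one of these is no longer answering the powered question.

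What is at stake is whether the primary comparison is the pre-named one for every outcome, or a different one for whichever outcomes fail a preliminary check.

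**Working it through.** **Step 1: which test the trial is powered on.** The plan states that "a total sample size of 40 participants would be needed" for "medium-sized effects defined as f = 0.25, with 80% power and alpha at .05". For a within-between interaction with k groups and m measurements:

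- λ = f²·N·m/(1 − ρ), df1 = (k − 1)(m − 1), df2 = (N − k)(m − 1).
- From the plan: f = 0.25, N = 40, k = 4, m = 3. Assumed: correlation ρ = 0.5 and sphericity.
- λ = 0.0625 × 40 × 3 / 0.5 = 15; df1 = 3 × 2 = 6; df2 = 36 × 2 = 72.
- Power = 0.805, and N = 40 is the smallest N that reaches 80%.

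The stated figure reproduces. (With ρ = 0, 0.3 or 0.7, N would be 76, 56 or 28, rounded to equal groups.) So the powered test is the interaction.

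**Step 2: how often a normality check would fail.** The article gives no outcome distributions, so every shape here is an assumption. Shapiro-Wilk at the 5% level, 1,500 simulated samples per cell, % rejecting:

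| Assumed shape | n = 30 | n = 40 | n = 60 |
|---|---|---|---|
| Donation, 10/20/30% at 0/15/30 NIS | 99.9 | 100 | 100 |
| Donation, 5/30/20% at 0/15/30 NIS | 99.2 | 100 | 100 |
| Donation, N(20,10) clipped to 0-30 | 58.7 | 77.2 | 96.1 |
| Donation, N(15,8) clipped | 4.5 | 5.1 | 11.1 |
| Donation, N(15,5) clipped | 6.5 | 5.1 | 5.9 |
| Stress, latent item mean 3.5 | 6.3 | 5.6 | 8.0 |
| Stress, latent item mean 2.5 | 22.2 | 32.9 | 51.1 |
| Stress, latent item mean 1.8 | 67.7 | 84.9 | 97.7 |
| Step rate, normal | 4.8 | 3.9 | 5.2 |

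Failure is near certain for spiked donations, likely for skewed donations or stress near its floor, and rare for central, spread-out responses.

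**Step 3: what each test then answers.** Simulated with 30 per arm, three visits and 3,000 trials per row, on a 0-30 outcome with mean 17, SD 9 before clipping and ρ = 0.5 (all assumed except the arm size, visits and bounds). % significant at an unadjusted 5%:

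| Scenario | ANOVA interaction | Mann-Whitney on pre-post change | Mann-Whitney at post | Friedman, one arm | Arms' Friedman verdicts differ |
|---|---|---|---|---|---|
| No effects | 5.2 | 5.3 | 5.0 | 5.7 | 10.9 |
| Both arms rise by 4.5 | 4.9 | 4.6 | 4.7 | 63.2 | 46.4 |
| Baseline gap of 4.5, no interaction | 5.2 | 4.9 | 44.2 | 5.3 | 9.3 |
| True effect of 7 | 83.2 | 76.4 | 80.4 | 96.0 | 91.4 |

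When both arms improve equally, separate within-arm tests disagree in 46.4% of trials. By symmetry about half of these, 46.4/2 = 23.2%, would favour the synchronous arm alone, with no difference between arms. The 44.2% for Mann-Whitney at post belongs to a baseline gap that was imposed. With no such gap, as randomisation gives on average, that test holds 5.0%.

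**The case against.** The strongest reply is that the plan does fix the test. The verb is *guide*, not decide. The sentence follows the descriptive, univariate and bivariate analyses and can be read as applying only to them. The ANOVAs are then named without condition, matching the power calculation. Which normality test and what threshold to use are details that an article may leave to an analysis plan.

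Part of this stands. The missing test and threshold are not faults here, and the narrow reading is possible. But the text does not say that the check stops short of the main analyses, and it speaks of each of the variables. The unresolved conflict is in what is stated, not in what is left out.

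A reader might also infer that the bounded primary outcomes will be sent to rank tests that cannot test arm by time. The documents do not support that:

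- **Failure is not assured.** It depends on shapes the article does not give (Step 2). Only two of the three primary outcomes are bounded. The closeness item with "seven Venn diagram-like pictures" is a secondary outcome, so it says nothing about the primary ones.
- **Some rank methods do test it.** Mann-Whitney on change tests a two-visit arm-by-time contrast at about 5% error, with 76% power against 83% for the ANOVA. Rank-based factorial methods also exist.
- **Within-arm testing is nowhere planned.** With 30 per arm and an equal standardised mean change of 0.3, 0.4 or 0.5, paired t tests have power 0.355, 0.563 and 0.754. The chance p(1 − p) of significance in the synchronous arm only is then 0.23, 0.25 and 0.19. The arithmetic is right, but it describes a fallback the article never names and leaves out the planned Holm adjustment.
- **No group adjustment is lost.** The planned ANOVA states no term for intervention group, so a switch cannot remove one.

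**Conclusion.** The point holds in a limited form. The article states a data-dependent rule based on variables rather than residuals, and does not reconcile it with the unconditional ANOVAs that follow or with the interaction used for power. If the rule reaches the primary analysis, the confirmatory test is chosen after the data are seen, and the most familiar alternatives do not test the powered effect.

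The chance of a switch at n = 60 runs from about 6% to 100% for the donation (11% upwards if the narrowest assumed shape is set aside) and from 8% to 98% for stress. These ranges rest on assumed distributions and on Shapiro-Wilk as the check. The 46% disagreement between within-arm tests shows what a poor fallback could do; it is not a forecast for this trial. The plan should be corrected before analysis. No sample-size figure changes.

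**What to change.** Replace the normality sentence with one that says:

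- the pre-named arm-by-time model is used for every primary and secondary outcome, whatever the normality result;
- residuals from that model are checked;
- where residuals are clearly non-normal, a bootstrap or permutation analysis of the arm-by-time contrast is reported as a sensitivity analysis.

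If the sponsor prefers to keep a rank-based fallback, it should be named in advance and contrast the arms over time, for example Mann-Whitney on change from baseline (at each later visit) or a rank-based factorial method. If the check was meant only for the descriptive and bivariate statistics, the sentence should say so.

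This defect does not require replacing the ANOVA with another class of model. The cost is one sentence and a little more computing, with no new data. The article places the analysis at the end of data collection and reports the fourth cycle as under way, so at that stage the change could still precede the analysis.

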### Objectives

The aim of this study is to assess the effects of group interpersonal synchrony on the prosociality and work-related stress of young autistic adults in their work environment. The primary objective is to determine whether a synchronized group intervention will have an immediate and/or long-term positive effect on participants’ prosociality and work-related stress. The secondary objectives are to determine: (1) Whether a synchronized group intervention will have an immediate and/or long-term positive effect on participants’ social closeness and sense of belonging, (2) Whether this effect will be influenced by participants’ need to belong as reported before the intervention, (3) How participants perceive the intervention as affecting their prosociality and work-related stress, and (4) In what ways the participants’ perception will contribute to a better understanding of the intervention effect.

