### Participants

This study will be conducted in collaboration with *Roim Rachok* Program (RRP) an innovative Israeli civilian program designed to integrate cognitively-abled young autistic adults first into the Israeli army work force, and later into the labor market [6]. As part of the program, before joining the army, the trainees take part in a professional 13 weeks course delivered by an interdisciplinary team that includes army officers and instructors, an occupational therapist, a speech therapist and an art therapist. The course content is composed of two main fields: (a) army related professional instruction (e.g., software programming, data analysis and image interpretation), and (b) integration into the army working environment. Trainees who successfully complete the course are inducted into the army as civilian volunteers for a four-month trial period. The trial period is designed to allow trainees to experience their future working environment before committing to long-term army service. Trainees who successfully complete the trial period can sign up for one more year of service with an annual option of extension, for up to three years. The RRP participants are integrated into the army corps with other soldiers who do not have developmental disabilities.

The sample for this study will be comprised of young adults enrolled in an RRP who fulfill the following criteria: **Inclusion criteria:** (a) Aged 18 to 25 when accepted to the program, since these age limits are defined as part of the admission requirements for the RRP. (b) Diagnosis of autism spectrum disorder: Participants must have an official diagnosis of an autism spectrum disorder as assessed by a child psychiatrist or clinical psychologist according to the DSM-V [1] before acceptance to the RRP. **Exclusion criteria:** Trainees with severe sensory impairments such as blindness or deafness and/or severe physical disability.

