The condition groups will be matched according to the following control variables: (a) gender (male/female); since there is diagnostic gender bias with respect to ASD [54] (b) army related profession (image interpretation/GIS/data analytics/software programming/electro-optics/data annotation) (c) handedness (right-handed/left-handed); since there is a larger distribution of left-handedness in the ASD population compared to the general population [55] (d) need to belong level (NTBL) (high/low). To control for handedness and NTBL during the randomization process, the following questionnaires will be administered to the participants: (a) The Hebrew adaptation of the Edinburgh Handedness questionnaire [56], the most common method for measuring handedness in individuals with Autism [57]. (b) The Hebrew adaptation of the Need to Belong (NTB) Scale [59] which comprises ten items rated on a 5-point Likert scale ranging from “Strongly Disagree” (1) to “Strongly Agree” (5). This scale has acceptable interitem reliability (the Cronbach’s alpha generally exceeds .80) and has been positively correlated with extraversion, agreeableness, and neuroticism and with having an identity that is defined in terms of social attributes [58]. NTBL(high/low) will be calculated using a cut-off of the NTB measure, so that participants with the 50% highest NTB score will be assigned a high NTBL and the rest will be assigned a low NTBL. After inclusion in the study and assessment of the control variables, participants will be assigned by the first author to one of the intervention conditions on an individual basis according to a computer-generated randomization procedure. The allocation ratio of the intended numbers of participants in the comparison groups will be 1:1 so that the number of participants assigned to the synchronous intervention will be similar to the number of participants assigned to the non-synchronous intervention. To this end, we will first create subgroups containing participants with same gender, army-related profession, handedness and NTBL. For each subgroup, alternate assignments will be made in random order. The order of subgroup assignments will also be determined randomly. For the first subgroup, we will use a simple coin flip randomization procedure to determine the intervention type to start assigning to. An overview of the study design is shown in Fig 3.

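### The primary two-way ANOVA treats baseline as an outcome level, and its interaction test does not separate the immediate from the long-term effect

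*Protocol article*

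**What the plan says.** All references are to the protocol article.

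- **Objectives.** The primary question is whether the synchronous intervention has an "immediate and/or long-term positive effect" on prosociality and work-related stress.
- **Quantitative data collection: Outcome variables.** Each outcome is measured three times: before the first session, after the last, and 17 weeks after the intervention ends. There are three primary outcomes.
- **Quantitative data analysis.** Effects over time ("at the end of the intervention and after 17 weeks) will be examined using a two-way mixed model ANOVA". A three-way version that adds need to belong serves the second secondary objective. Holm's procedure is applied. SPSS 27 is named, but no procedure within it and no rule for missed measurement visits. The one exclusion rule concerns session attendance.
- **Sample size.** The calculation was made "using a repeated measure, within-between interaction ANOVA with four groups and three measurements", to "detect medium-sized effects defined as f = 0.25" "with 80% power and alpha at .05".
- **Study design.** "The condition groups will be matched according to the following control variables": gender, profession, handedness and need-to-belong level. A two-way model has room only for arm and time, so none of the four is in the primary model. Need to belong enters only the three-way model.

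**The concern.** Three features of the stated model deserve attention.

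1. **Baseline as a response.** With baseline as a level of time, the arm effect at a later occasion is in substance a difference in change from baseline. In a randomised comparison, using the same baseline value as a covariate estimates the same effect with smaller variance at any correlation below 1.
2. **A test that does not match the objective.** The objective names two times and a direction. The interaction pools both times and is undirected.
3. **Possible loss of observed data.** A classical repeated-measures ANOVA needs all three values. A trainee seen at the end of the intervention but not at 17 weeks would then drop out of the immediate comparison too.

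At stake are power, in a trial of 60, and the ability to say which part of the primary objective a significant result supports.

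**Working it through.** **Inputs from the article.** 60 participants, 30 per arm; three occasions; 5% level; f = 0.25. The Sample size section also says "an effect defined as d = 0.25 may be expected". The two are different effects, since f = 0.25 corresponds to d = 0.5 for two groups. The calculation used f = 0.25, so 0.5 SD is used here.

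**Assumptions.** Correlation ρ between any two occasions of 0.3, 0.5 or 0.7, with equal variances. The article gives no correlation.

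**1. The plan's own figure.** For k groups and m occasions, λ = f²·N·m/(1−ρ), df1 = (k−1)(m−1) and df2 = (N−k)(m−1). With k = 4, m = 3, N = 40 and ρ = 0.5: λ = 0.0625 × 40 × 3 / 0.5 = 15, df = 6 and 72, power 0.805. N = 36 gives 0.749. The stated total of 40 therefore reproduces, and it rests on a three-occasion interaction in which baseline is one of the occasions.

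**2. Cost of baseline as a level of time.** Per-person variance of the arm contrast at one later occasion, in SD² units, is 2(1−ρ) on change and 1−ρ² adjusted for baseline. The ratio is (1+ρ)/2. Power is from the noncentral t with SE = √(2V/30), noncentrality 0.5/SE, and 58 df (change) or 57 df (adjusted), two-sided 5%, no missing data.

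| ρ | V, change | V, adjusted | Ratio | Power, change | Power, adjusted |
|---|---|---|---|---|---|
| 0.3 | 1.40 | 0.91 | 0.65 | 0.36 | 0.51 |
| 0.5 | 1.00 | 0.75 | 0.75 | 0.48 | 0.59 |
| 0.7 | 0.60 | 0.51 | 0.85 | 0.69 | 0.76 |

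The analysis sentence itself names only the two later occasions. If the ANOVA were meant to use those alone, baseline would not be used at all. The variance would be 1, and adjustment would save ρ² = 9%, 25% or 49%.

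**3. What the interaction can tell.** For arm differences δ at the three occasions, λ = (N/4)·Σ(δ−mean δ)²/(1−ρ).

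- Sustained effect, δ = (0, 0.5, 0.5): mean 1/3, sum of squares 1/9 + 1/36 + 1/36 = 1/6.
- Immediate effect only, δ = (0, 0.5, 0): mean 1/6, sum of squares 1/36 + 1/9 + 1/36 = 1/6.
- Harm of the same size: signs reversed, again 1/6.

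All give λ = 15 × (1/6)/0.5 = 5 at ρ = 0.5 and the same power, 0.49. The test responds identically to a lasting benefit, a transient benefit and harm.

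**4. Missed visits, if the fit is classical.** Assumed values missing completely at random, 0.5 SD at both later occasions, 3,000 simulated trials per scenario. The adjusted analysis uses everyone seen at the end of the intervention.

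| Missing at post / 17 weeks | Complete of 60 | Complete-case interaction, ρ = 0.3 / 0.5 / 0.7 | Adjusted, all post data |
|---|---|---|---|
| 5% / 15% | about 48 | 0.31 / 0.40 / 0.62 | 0.49 / 0.58 / 0.73 |
| 10% / 20% | about 43 | 0.27 / 0.36 / 0.55 | 0.45 / 0.53 / 0.69 |

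These gaps combine baseline adjustment with retention of partial data.

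**5. Cost of the alternative.** An unhelpful covariate inflates variance by about 57/(57−q) for q degrees of freedom. The need-to-belong score alone (q = 1) gives 1.02, and power at ρ = 0.5 goes from 0.594 to 0.586. All balancing factors plus cycle (q about 11: gender 1, handedness 1, need to belong 1, profession 5, cycle 3) give 57/46 = 1.24 and power of about 0.50, which cancels the gain unless they predict outcome.

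Two contrasts for three primary outcomes make six tests. At the strictest Holm step, taking the primary outcomes as the family, an adjusted contrast at 0.05/6 has power 0.25 / 0.32 / 0.50. The interaction at 0.05/3 has 0.22 / 0.32 / 0.56.

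**The case against.** **Listwise deletion is not stated.** This is correct. SPSS can fit a mixed model by likelihood and keep partial data, and missing-data handling may sit in an analysis plan that is not shown. The three-measurement sizing suggests the classical form but does not fix it, so step 4 is conditional.

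**Success-dependent follow-up.** A reader might infer that only successful trainees are measured at 17 weeks, because "Trainees who successfully complete the course are inducted into the army". That sentence says who is inducted, not who is followed. The data-collection section says each participant is measured at all three times. Selection at follow-up is possible but undocumented.

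**A larger loss of power.** A reader might take the gap between 60 recruited and 40 needed as 20 people missing only the last visit, which would bring the change contrast to 0.34 at ρ = 0.5. The article gives no dropout rate, and that margin must also cover full dropouts and trainees with too few sessions. The scenario is not the plan's.

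**Balancing factors.** To say the analysis ignores them is too broad, since need to belong is in the three-way model. Omitting balanced factors is typically conservative, not biasing, and no gain from them can be computed from the article.

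**An omnibus test suits an and/or objective, and contrasts are ordinary later detail.** This stands in part. With complete data the planned interaction is a valid randomised comparison. But it carries no direction, and the objective asks for a positive effect.

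**The gain shrinks under Holm.** This also stands: at the strictest step the power advantage disappears at ρ = 0.5 and reverses at 0.7. The comparison is between different questions, though. To say which time shows an effect, the ANOVA would need the same six contrasts, with larger variance.

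**Conclusion.** The point holds as one of efficiency and of fit between test and objective. No figure in the plan is shown to be wrong by it, and no bias is shown. On the natural reading, baseline is an outcome level, which forgoes a 15–35% reduction in variance for correlations of 0.7 down to 0.3. In power for 0.5 SD at one time, that is 7 to 15 percentage points at an unadjusted 5%. The undirected 2-df interaction cannot distinguish a lasting benefit, a transient benefit or harm. Loss of end-of-intervention data through a missed 17-week visit follows only if the model is fitted classically. The correlations, the 0.5 SD difference and the missingness rates are assumptions. If the smaller d = 0.25 is the true target, adjustment still helps, but power is low either way: 0.17 / 0.20 / 0.27 adjusted against 0.13 / 0.16 / 0.23 on change.

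**What to change.** In Quantitative data analysis, replace the two-way ANOVA with wording such as:

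*Each primary outcome will be analysed with a likelihood-based linear mixed model of the two post-baseline occasions, using all observed data. Fixed effects are arm, time, arm by time, the baseline value of the outcome, baseline by time, and the continuous need-to-belong score. Within-person covariance is unstructured. The two contrasts are the arm difference at the end of the intervention and the arm difference at 17 weeks. All contrasts for the primary outcomes are tested within the Holm procedure.*

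Use the same model for the first secondary objective. Add other balancing factors only as far as is feasible, for example gender. Their prognostic strength is undocumented, and fitting all of them plus cycle could cost the gain.

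The cost is a few degrees of freedom and six Holm-adjusted primary tests instead of three. SPSS 27 can fit the model and no new data are needed. The article says analysis follows the end of collection, and the fourth cycle was still running, so the wording can be settled before the data are analysed.
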